## Abstract

**Background:**

Patients with chronic kidney disease (CKD) are at risk of progression to end-stage renal disease and cardiovascular disease. Data from other populations and animal experiments suggest that neprilysin inhibition (which augments the natriuretic peptide system) may reduce these risks, but clinical trials among patients with CKD are required to test this hypothesis.

**Methods:**

UK Heart and Renal Protection III (HARP-III) is a multicentre, double-blind, randomized controlled trial comparing sacubitril/valsartan 97/103 mg two times daily (an angiotensin receptor–neprilysin inhibitor) with irbesartan 300 mg one time daily among 414 patients with CKD. Patients ≥18 years of age with an estimated glomerular filtration rate (eGFR) of ≥45 but <60 mL/min/1.73 m^2^ and urine albumin:creatinine ratio (uACR) >20 mg/mmol or eGFR ≥20 but <45 mL/min/1.73 m^2^ (regardless of uACR) were invited to be screened. Following a 4- to 7-week pre-randomization single-blind placebo run-in phase (during which any current renin–angiotensin system inhibitors were stopped), willing and eligible participants were randomly assigned either sacubitril/valsartan or irbesartan and followed-up for 12 months. The primary aim was to compare the effects of sacubitril/valsartan and irbesartan on measured GFR after 12 months of therapy. Important secondary outcomes include effects on albuminuria, change in eGFR over time and the safety and tolerability of sacubitril/valsartan in CKD.

**Results:**

Between November 2014 and January 2016, 620 patients attended a screening visit and 566 (91%) entered the pre-randomization run-in phase. Of these, 414 (73%) participants were randomized (mean age 63 years; 72% male). The mean eGFR was 34.0 mL/min/1.73 m^2^ and the median uACR was 58.5 mg/mmol.

**Conclusions:**

UK HARP-III will provide important information on the short-term effects of sacubitril/valsartan on renal function, tolerability and safety among patients with CKD.

## INTRODUCTION

Chronic kidney disease (CKD) affects between 2 and 17% of the general population (depending on the country) [1, 2] and is associated with increased risks of progression to end-stage renal disease (ESRD) and morbidity and mortality from cardiovascular disease (CVD) [3, 4]. Renin–angiotensin system (RAS) inhibitors [angiotensin-converting enzyme inhibitors (ACEis) and angiotensin receptor blockers (ARBs)] have been shown to reduce the risk of ESRD in patients with proteinuric CKD [5–8], but despite such treatments, patients remain at significant risk of progression to ESRD and CVD.

The natriuretic peptide (NP) system is a neurohormonal system that has a variety of potentially beneficial functions, including natriuresis, diuresis, vasodilatation and counterregulation of RAS [9, 10]. The NP system can be augmented by inhibiting the main enzyme responsible for degrading NPs, namely neprilysin [or neutral endopeptidase (NEP)] [10]. NEP is a membrane-bound zinc-containing metalloproteinase [11] that also degrades other peptides, including angiotensin II, bradykinin, endothelin and substance P [12]. However, isolated NEP inhibition (NEPi) leads to reflex RAS activation, and inhibits angiotensin II breakdown (counteracting any potentially beneficial effects) and therefore NEPi must be combined with RAS inhibition.

As NEPi and ACEi both inhibit bradykinin degradation, their combination is associated with substantially elevated bradykinin levels that cause unacceptable rates of angioedema [13]. ARBs do not inhibit bradykinin degradation and can be safely combined with NEPi [creating a new class of drugs called angiotensin receptor–neprilysin inhibitors (ARNis)]. Sacubitril/valsartan (previously known as LCZ696) is the first drug in this new class, combining valsartan with sacubitril [(AHU377) a prodrug that is metabolized via esterases to the active NEPi sacubitrilat (LBQ657)]. Sacubitril/valsartan 97/103 mg provides equivalent plasma concentrations of valsartan as oral valsartan 160 mg [14].

In a 5/6 nephrectomy model, treatment with combined NEP/RAS inhibition was associated with greater reductions in proteinuria and glomerulosclerosis compared with RAS inhibition alone [15, 16]. Micropuncture studies also demonstrated NEPi led to greater reductions in capillary glomerular pressure [15]. Among patients with heart failure, trials comparing sacubitril/valsartan with either ACEi or ARB have suggested that the estimated glomerular filtration rate (eGFR) of patients allocated sacubitril/valsartan declined less than those assigned ACEi or ARB [17, 18]. Sacubitril/valsartan also reduced blood pressure more than equivalent doses of valsartan in trials among patients with elevated blood pressure [19]. Trials in heart failure populations suggest NEPi might increase albuminuria [18, 20], but this effect was not observed in patients with hypertension [19] and baseline albuminuria was very low in all these trials. Overall, these data raise the hypothesis that treatment with an ARNi may be superior to either ACEi or ARB alone in slowing the progression of CKD.

The United Kingdom (UK) Heart and Renal Protection III(HARP-III) trial (ISRCTN11958993) was designed to provide information on the short-term efficacy (in terms of effect on renal function), tolerability and safety of sacubitril/valsartan among patients with CKD. The trial will also assess the effects of sacubitril/valsartan on albuminuria, blood pressure and biomarkers of kidney and cardiac damage.

## MATERIALS AND METHODS

### Study design

UK HARP-III is a double-blind, multicentre, randomized controlled trial comparing sacubitril/valsartan 97/103 mg two times daily versus irbesartan 300 mg one time daily among at least 400 participants ≥18 years of age with stages 3 and 4 CKD. Irbesartan 300 mg was selected as the comparator, as it has been shown to reduce the risk of ESRD among patients with diabetic kidney disease and is licensed for the treatment of proteinuric CKD [6, 21]. Participants were randomly allocated to receive sacubitril/valsartan or irbesartan and will be followed up for 1 year (Figure 1). The primary aim of UK HARP-III is to assess the effect of sacubitril/valsartan 97/103 mg two times daily versus irbesartan 300 mg one time daily on measured glomerular filtration rate (mGFR) at 12 months. Important secondary outcomes include the effect on urine albumin:creatinine ratio (uACR) and eGFR. All the secondary and tertiary assessments are shown in Figure 2 and further details are available in the data analysis plan (see Supplementary data). A summary of substantial amendments to the protocol is provided in the Supplementary data.

**FIGURE 1 GFW321F1:**
[figure not shown]
UK HARP-III trial design.

**FIGURE 2 GFW321F2:**
[figure not shown]
UK HARP-III trial outcomes.

### Eligibility

To fulfil the inclusion criteria, patients need to be ≥18 years of age and have either an eGFR ≥45 but <60 mL/min/1.73 m^2^ with a uACR >20 mg/mmol or eGFR ≥20 but <45 mL/min/1.73 m^2^ (regardless of uACR). The exclusion criteria were designed to identify patients for whom the safety of sacubitril/valsartan or irbesartan may have been a concern. The full eligibility criteria are shown in Figure 3.

**FIGURE 3 GFW321F3:**
[figure not shown]
Inclusion and exclusion criteria. ALT, alanine aminotransferase; AST, aspartate aminotransferase; ULN, upper limit of normal.

### Study enrolment and randomization

#### Identification and invitation

After relevant ethics [Nottingham Research Ethics Committee 2 (13/EM/0434)] and regulatory approvals had been obtained, sites were established in UK renal units. Site staff identified potentially eligible patients from hospital electronic databases, mailed these individuals an invitation letter and a copy of the patient information sheet and called them ∼1 week later to discuss the trial in more detail, answer any questions they might have and to see whether they were interested in participating. Those individuals interested in participating were invited to attend a screening visit.

#### Screening

At the screening visit, eligibility was assessed and written informed consent was obtained from eligible individuals. All data were recorded directly into a bespoke Internet-based electronic case report form system. Relevant details of their medical history (including primary renal diagnosis, presence of diabetes mellitus and prior CVD) were recorded by trained research nurses and their height, weight and blood pressure were measured. Blood pressure was measured and recorded three times using an Omron M6 automated digital sphygmomanometer after sitting for at least 5 minutes. Willing and eligible patients entered the pre-randomization run-in phase. Samples of blood and urine were sent to the local hospital laboratory for confirmation of eligibility. If the results were considered inaccurate (e.g. haemolysed sample) by the local study staff the samples could be repeated once, but if the results did not confirm eligibility the participant was withdrawn from the run-in phase.

#### Pre-randomization run-in

The aims of the pre-randomization run-in phase were (i) to ‘wash out’ any ACEi prior to introduction of NEPi, (ii) to allow a comparison of the acute effects of the study treatments on GFR and (iii) to reduce the rate of post-randomization discontinuation of study treatment and to produce a consequent improvement in the trial's statistical sensitivity [22]. Following the screening visit, any current ACEi and/or ARB that the participant was taking was stopped and the participant entered the 4- to 7-week single-blind pre-randomization run-in phase, during which they were asked to take one placebo sacubitril/valsartan tablet and one placebo irbesartan capsule once daily. If elevated blood pressure became a concern during the run-in phase, local investigators were advised to titrate up or start additional anti-hypertensive medications, but to avoid an ACEi, ARB or direct renin inhibitor (DRI). The choice of additional anti-hypertensive therapy remained at the discretion of the responsible clinician. Participants could withdraw from the trial for any reason during this run-in phase. Participants who did not withdraw returned 4–7 weeks later and had their GFR measured and attended a randomization visit. GFR was measured using a standard ^51^Cr-EDTA technique, although if this was not available at the site, other methods (^99m^Tc-DTPA or iohexol) could be used with the agreement of the coordinating centre. In willing participants, a 24-hour collection of urine for albumin and sodium quantification was also obtained.

#### Randomization visit

Participants were not eligible for randomization if the mean of their second and third measurements of systolic blood pressure was <110 mmHg (or <130 mmHg with symptoms of hypotension) or if they reported an adverse event they believed to be related to their run-in treatment. Participants who remained willing and eligible were then randomly allocated in a 1:1 ratio to receive either sacubitril/valsartan or irbesartan. Participants were randomized by an Internet-based system using a minimization algorithm to ensure balance of important predictors of renal progression, including age, sex, systolic blood pressure, eGFR, uACR and the presence or absence of diabetes mellitus.

At the randomization visit, run-in treatment was collected and willing and eligible participants were issued two bottles of study treatments: one containing sacubitril/valsartan 97/103 mg or placebo tablets and the other containing irbesartan 150 mg or placebo capsules (therefore a double-dummy technique to protect blinding). Participants were initially instructed to take one tablet and one capsule daily in the morning (i.e. either sacubitril/valsartan 97/103 mg plus placebo irbesartan or placebo sacubitril/valsartan plus irbesartan 150 mg). Blood and urine samples were collected for the local analysis of creatinine, electrolytes, liver function tests and uACR and others were prepared for central analysis (Table 1).

**Table 1 GFW321TB1:** Planned central laboratory blood and urine analyses

Analyte	Time point			
	Randomization	3 months	6 months	12 months
EDTA plasma samples				
Creatinine	▪	▪	▪	▪
Albumin	▪		▪	▪
Troponin-I	▪		▪	▪
NT-proBNP	▪		▪	▪
CRP	▪		▪	▪
IL-6	▪		▪	▪
*Urine samples*				
Albumin:creatinine ratio	▪	▪	▪	▪
KIM-1	▪		▪	▪
NGAL	▪		▪	▪
cGMP	▪		▪	▪
β-2-microglobulin	▪		▪	▪
Retinol binding protein	▪		▪	▪

NT-proBNP, N-terminal prohormone brain natriuretic peptide; CRP, C-reactive protein; IL-6, interleukin 6; KIM-1, kidney injury molecule 1; NGAL, neutrophil gelatinase-associated lipocalin; cGMP, cyclic guanosine monophosphate.

### Post-randomization follow-up

Randomization is now complete and all participants are in follow-up. In order to check potassium and renal function after starting study treatment, participants attend their study clinic or local primary care physician at 2 weeks after randomization for a blood sample. If these results are satisfactory, study treatments are increased to either sacubitril/valsartan 97/103 mg two times daily plus two capsules of placebo irbesartan one time daily or one tablet of placebo sacubitril/valsartan two times daily plus irbesartan 300 mg one time daily.

#### Follow-up assessments

Study follow-up visits are scheduled at 1, 3, 6, 9 and 12 months after randomization. At all visits, study staff systematically seek the information on all serious adverse events, any non-serious adverse events considered by participants to be related to study treatment; and on symptoms of hepatitis. Compliance with study treatment is assessed and participants unable to tolerate the maximum dose of study treatments are encouraged to continue on the lower dose of study drug (i.e. sacubitril/valsartan 97/103 mg or irbesartan 150 mg daily) for the remainder of the trial. If relevant, a reason for discontinuation or dose reduction is recorded. Participants prescribed contraindicated medications (ACEi, ARB or DRI) have their randomized treatment stopped. Weight and blood pressure are measured (three times after sitting for at least 5 minutes) at all visits. In both treatment groups, blood pressure is to be controlled according to the Kidney Disease: Improving Global Outcomes guidelines [23], with the initiation and choice of additional anti-hypertensive treatment being at the discretion of the responsible clinician. Within the 2 weeks before their 12-month visit participants have their second GFR measurement (using the same method as at baseline). Copies of results of both measurements of GFR are sent to the coordinating centre so the results entered by site staff can be verified by clinical study staff blind to the treatment allocation.

#### Biological samples and safety monitoring

At each follow-up visit, blood and urine samples are sent to the local hospital laboratory for creatinine, electrolytes, liver function tests (bilirubin, alanine or aspartate transaminase and alkaline phosphatase) and uACR. In addition, at the 3-, 6- and 12-month visits, samples are also taken for central analysis. EDTA samples are centrifuged and the plasma aliquoted into Cryovials, which are stored locally (with Cryovials of urine) at or below −20°C prior to transfer to the central laboratory in Oxford, UK, where they are stored at −80°C. The main plasma analytes measured at the central laboratory are creatinine, cardiac and inflammatory biomarkers and the urine analytes include albumin and markers of tubular damage and function [including kidney injury molecule 1, neutrophil gelatinase-associated lipocalin, β2-microglobulin and retinol binding protein; Table 1]. Participants are asked not to take their morning dose of study treatment on the day of their 3-month visit (at this visit only) and the date and time of the last dose is recorded, as these samples are to be used for pharmacokinetic analyses.

The results of local samples are entered into the trial database once available and reviewed daily by a trained clinician at the coordinating centre. If the potassium is >5.5 mmol/L, alanine or aspartate transaminase >2× the upper limit of normal or if the eGFR has fallen >25% from the previous value, then the trial protocol provides advice on further tests and study treatment (see Supplementary data).

### Monitoring

Prior to starting recruitment, study staff received training in the study procedures and the web-based data collection system at the coordinating centre. Recruitment rates, adherence to trial procedures and completeness of follow-up data are monitored closely by staff at the coordinating centre. All sites have at least one on-site monitoring visit, with further visits as indicated by the results of central monitoring of the data. An independent data monitoring committee (see Supplementary data) regularly reviews unblinded interim analyses of all relevant data.

### Statistical considerations

#### Sample size

The chief aim of this study is to compare mGFR between the two treatment groups at the final follow-up visit. Analysis of covariance (ANCOVA) compares mean follow-up mGFR between treatment groups after adjustment for baseline mGFR [24]. Assuming a between-person standard deviation (SD) in mGFR of 15 mL/min/1.73 m^2^ and a correlation between an individual's baseline and follow-up mGFR of 0.8, randomization of 400 participants will provide at least 80% power (at 2 P = 0.05) to detect a difference in mGFR at the final follow-up (adjusted for baseline values) of 3 mL/min/1.73 m^2^ (the chosen minimum clinically meaningful difference), even if 15% of participants discontinue allocated study treatment [20].

#### Statistical analysis

All analyses will involve comparing outcomes during the scheduled treatment period among all those participants allocated at randomization to receive sacubitril/valsartan 97/103 mg two times daily versus all those allocated to receive irbesartan 300 mg one time daily [i.e. intention-to-treat (ITT) analyses] [25, 26]. Comparisons of continuous outcomes (including the primary outcome) between the allocated treatment arms will be performed using ANCOVA adjusted for each patient's value at baseline [27]. If continuous outcomes are not normally distributed, then appropriate transformations (e.g. log transformation) will be made. Multiple imputation techniques will be used to account for any missing data in the primary and secondary outcomes [28]. Further details are provided in the data analysis plan (see Supplementary data).

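### The stated primary ANCOVA names none of the minimisation factors; if they predict 12-month mGFR beyond baseline mGFR, precision is lost and the test is conservative

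*Protocol article*

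**What the plan says.** **Allocation** (protocol article, Randomization visit). Patients were "randomly allocated in a 1:1 ratio to receive either sacubitril/valsartan or irbesartan". The method is described as "using a minimization algorithm to ensure balance of important predictors of renal progression". Six such factors are then listed: "including age, sex, systolic blood pressure, eGFR, uACR and the presence or absence of diabetes mellitus".

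**Analysis** (Statistical analysis). One model is given for every continuous outcome: "Comparisons of continuous outcomes (including the primary outcome) between the allocated treatment arms will be performed using ANCOVA adjusted for each". The sentence ends by naming the participant's own baseline measurement as the adjustment.

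**Power** (Sample size). The calculation rests on the same model, which "compares mean follow-up mGFR between treatment groups after adjustment for baseline mGFR".

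Neither statistical section mentions the minimisation factors. Both Study design and Statistical analysis refer to a data analysis plan in the supplementary material for further detail. That plan is not at hand.

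**The concern.** Minimisation removes most of the chance imbalance between arms in the factors it uses. If those factors are prognostic, the treatment estimate varies less from trial to trial than under simple randomisation. A model without them still counts their contribution as residual noise. Its standard error then describes a less efficient design than the one that was run: the interval is too wide on average and the test rejects a true null in fewer than 5% of trials.

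Precision is what is at stake, not validity. Planned power has little margin, and recruitment is closed, so the analysis model is one of the few places where precision can still be gained. The spread of uACR is wide (Table 3: median 58.5 mg/mmol, interquartile range 12.5 to 156.3), and baseline mGFR does not measure it.

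**Working it through.** **Inputs from the article (Sample size):** SD of mGFR 15; correlation of baseline with follow-up 0.8; 400 randomised, so 200 per arm; two-sided 0.05; difference 3; 15% discontinuing. From Results: 414 randomised.

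**Input not in the documents:** p, the share of the variance remaining after baseline mGFR that the minimisation factors explain (their partial R²). It is assumed here to lie between 0 and 20%.

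**Step 1: reproduce the stated power.**
- Residual SD = 15 × √(1 − 0.8²) = 9.0.
- SE of the difference = 9 × √(2/200) = 0.90.
- If those who stop treatment lose the whole effect, the intention-to-treat difference is 3 × 0.85 = 2.55.
- Power = Φ(2.55/0.90 − 1.96) = Φ(0.873) = 80.9%, which agrees with the stated minimum of 80%.
- The number needed for 80% is 196 per arm (392 in all). With 414 randomised the power is 82.2%.

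**Step 2: add the factors.** The residual SD becomes 9 × √(1 − p), so:
- adjusted SE = 0.90 × √(1 − p);
- adjusted power = Φ(2.55/adjusted SE − 1.96).

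**Step 3: the baseline-only model under minimisation.** It goes on reporting an SE of 0.90. If balance on the factors is perfect, the true SE is the adjusted one. Then:
- overstatement of the SE = 1/√(1 − p) − 1;
- true type I error = 2 × Φ(−1.96/√(1 − p));
- power of the baseline-only test = Φ((2.55 − 1.96 × 0.90)/(0.90 × √(1 − p))).

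| Assumed p | Adjusted SE | Adjusted power | Baseline-only SE too large by | Baseline-only type I error | Baseline-only power |
|---|---|---|---|---|---|
| 0 | 0.900 | 80.9% | 0% | 5.0% | 80.9% |
| 2% | 0.891 | 81.7% | 1.0% | 4.8% | 81.1% |
| 5% | 0.877 | 82.8% | 2.6% | 4.4% | 81.5% |
| 10% | 0.854 | 84.8% | 5.4% | 3.9% | 82.1% |
| 20% | 0.805 | 88.6% | 11.8% | 2.8% | 83.6% |

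The last three columns need near-perfect balance. Minimisation itself helps the baseline-only test a little. The gain from adjustment is therefore best read against the last column: about 1, 3 and 5 points at p = 5, 10 and 20%.

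**Step 4: check by simulation.** Minimised allocation was simulated for 400 patients and six factors, with an assumed biased coin of 0.9 and 1,500 runs per setting. Simulation error is about 0.6 points on type I error and 1 point on power.
- p = 10%: the baseline-only model reported an SE of 0.90 against an actual spread of about 0.855. Type I error was 2.9% without the factors and 4.9% with them; power was 81.9% and 84.7%.
- p = 20%: type I error was 2.8% and 3.9%; power was 83.8% and 89.1%.
- p = 0 and 5%: no clear difference between the models.

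The direction agrees with the formulas. The simulated type I errors are too noisy to support decimals.

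**The case against.** The strongest objection is that the article condenses a plan that is not shown. It does not say that baseline is the sole covariate, and a full covariate list is commonly left to the analysis plan. This stands in part. A reader might infer that the trial will adjust for nothing else and will ignore all six factors, but the documents do not establish that. They do write down a primary model in two places, each with one covariate, and base the power on it. The point concerns that stated choice.

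Four further limits stand:

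- **Not all six factors are unaccounted for.** Baseline mGFR measures the same quantity as eGFR. For the eGFR and uACR outcomes, the outcome's own baseline value is itself a minimisation factor.
- **The size may be near nil.** Baseline mGFR already removes 0.8² = 64% of the variance. The article calls the factors predictors of progression; it does not say how much they add once baseline mGFR is known, nor that uACR adds most.
- **The type I error figures are conditional.** The article gives no categories, weights or random element for the algorithm, so the balance achieved is unknown.
- **A reader might infer that this trial's P value will be too large, or that its power is inadequate.** Neither follows. The overstatement holds on average over repeated trials, not necessarily in this one, and the power claim reproduces under the baseline-only model.

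**Conclusion.** The point holds as a modest matter of efficiency. The primary model as written leaves out age, sex, systolic blood pressure, uACR and diabetes, although allocation was constrained on them. If they carry information on 12-month mGFR beyond baseline mGFR, the model-based SE is too large on average, the test is conservative and some precision is given up. There is no bias and no excess of false positives.

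The mechanism is secure; the size is not. It depends wholly on p, which the documents do not give: nothing is lost at p = 0, very little at 2%, and a worthwhile amount only towards 10% or more. The case for acting is that the change costs almost nothing, not that the stated analysis is invalid.

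**What to change.** Before unblinding, state the primary model as an ANCOVA of 12-month mGFR on treatment, baseline mGFR and every factor that the minimisation used. The six named are introduced as examples, so the list should be confirmed. Enter factors as continuous where they were recorded so, with uACR on the log scale.

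Say how missing baseline covariates are handled. Table 3 shows 27 participants without uACR and 5 without eGFR. The documents do not say which values the minimisation used. If those values are held, use them; otherwise extend the planned multiple imputation to these covariates so that nobody is dropped.

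Use the same covariates for the key secondary continuous outcomes, and keep the baseline-only model as a sensitivity analysis. If the data analysis plan already specifies this, the only change needed is to the article's description of the model.

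Cost: a sentence or two in the plan and about six degrees of freedom out of 414. The factors were already collected for allocation. If p is close to zero, adjustment gains nothing and loses next to nothing.
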